#### Blinding

Due to the study design, the patients and the study staff conducting the VR sessions are not blinded. However, the individuals directly involved in the treatment of patients are blinded to the intervention. The personnel assessing the clinical endpoints that are not collected during the VR sessions are blinded to the intervention.

#### Confounding factors

Performance bias is reduced by using standardised guidance for study staff.

### Sample size calculation

The feasibility study is being carried out with the aim to investigate the clinical and feasibility endpoints of the proposed intervention. Since there is no existing data to enable precise sample size calculations, we adhered to recommendations for sample size calculations in pilot trials. The current postoperative mean length of stay in our own patient population is approx. Thirteen days with a standard deviation of approx. 9.5. A targeted reduction in the length of stay by 2 days would result in a standardized effect size of 0.21. Whitehead et al. recommend a case number of *n* = 28 per group for pilot studies with a standardized effect size of 0.2 and a later planned study with a power of 90% [39]. In order to account for dropouts, e.g. due to non-completed questionnaires or study exclusions, 3 additional patients per group will be recruited. This results in a total number of 62 patients (31 per group).

### Data collection

All data will be documented in hard copy case report forms. The completed CRFs will be reviewed by one of the investigators or an authorized sub-investigator. All data collected according to the study protocol will be manually transferred from the case report forms to an electronic SPSS file (IBM, Armonk NY, USA). Regular reviews of the correct data transfer are conducted by assessors at the study site. The electronic data will be stored in a protected folder on a server at University Hospital Augsburg. Paper-based data are stored in a locked office at the study site.

### Pseudonymisation

Data evaluation is carried out in a pseudonymised form. For this purpose, a randomly generated numerical four-digit code is assigned to each participant. Access to the original data and the pseudonymisation lists is restricted to the staff of the Department of General-, Visceral and Transplant Surgery at the University Hospital Augsburg. The data will be deleted as soon as they are no longer used for research.

### Data analysis plan

Continuous data will be presented as mean ± standard deviation or median with an interquartile range, depending on the distribution. Categorical data will be presented as numbers with percentages. Approximately, normally distributed continuous variables will be compared using the independent *t* test. Non-normally distributed continuous variables will be compared using the Mann–Whitney *U* test. Categorical data will be compared using the *χ*^2^ test. Fisher’s exact test will be used for categorical data if the requirements for *χ*^2^ test are not met. A two-sided *P* < 0.05 is considered significant.

The basic questionnaire used for this study is the validated and standardised EQ-5D-5L health questionnaire of the EuroQol Research Foundation. It will be scored and reported as recommended in the EQ-5D-5L user guide. A questionnaire with additional questions on patient satisfaction (EORTC IN-PATSAT 32) will also be analysed.

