### Rationale for a pilot trial

Currently, there are no data on the use of VR-based fitness games in the early postoperative period after colorectal surgery. There are no data available to estimate the effect size and thus enable a high-quality sample size calculation. Therefore, this pilot study aims to investigate the clinical and feasibility endpoints of the proposed intervention. Our aim is to assess, whether the design and protocol used will prove effective in terms of patient recruitment, patient compliance and patient acceptance of the intervention, and whether the intervention will have an impact on quality of life, general health, sleep, patient satisfaction, length of stay and complication rates.

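### The either/or summary rule would probably leave out the mean difference and SD of length of stay that the pilot was sized on, and clinical P values carry no exploratory label

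*Protocol article*

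**What the plan says.** The Data analysis plan gives one general rule for continuous outcomes: "Continuous data will be presented as mean ± standard deviation or median with an interquartile range, depending on the distribution". The choice of test follows the same split: "Approximately, normally distributed continuous variables will be compared using the independent *t* test", and "Non-normally distributed continuous variables will be compared using the Mann–Whitney *U* test". The threshold is then set for everything: "A two-sided *P* < 0.05 is considered significant". The section has no exploratory label, no multiplicity rule and no between-group estimate with a confidence interval.

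The Rationale for a pilot trial states "There are no data available to estimate the effect size and thus enable a high-quality sample size calculation". The Sample size calculation nevertheless rests on a mean and an SD. It begins "The current postoperative mean length of stay in our own patient population is approx" and goes on to give thirteen days with an SD of about 9.5, a target reduction of 2 days, a standardised effect of 0.21, and 28 + 3 = 31 patients per group. The Discussion justifies the control arm partly by the better estimate of effect size it should allow.

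Clinical outcomes lists five items: health status and distress (each preoperatively, at 7 days and at 30 days), complications (number and severity, by Clavien-Dindo and the Comprehensive Complication Index), length of stay, and satisfaction at discharge.

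**The concern.** A pilot meant to inform a later trial should deliver the quantities that trial is planned with. Here those are a difference in mean length of stay and an SD. The stated rule makes their reporting depend on the shape of the data, and the protocol's own figures indicate that the shape will point to the median.

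The plan also attaches the word significant to any clinical comparison with P below 0.05, in a study far too small to test its 2-day target. A chance result could then be read as evidence of efficacy. A true but overestimated difference could be carried into the next sample size calculation.

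**Working it through.** **Inputs.** From Sample size calculation: mean 13 days, SD 9.5, difference 2 days, 28 per group plus 3 for dropout. From Data analysis plan: two-sided 0.05 per test. From Clinical outcomes: the five outcomes and their time points.

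**The plan's own figures.** 2/9.5 = 0.2105, which rounds to the stated 0.21. 28 + 3 = 31, and 2 × 31 = 62. Minimising pilot plus main-trial size at an effect of 0.2 and 90% power (non-central t allowance for the uncertainty of the pilot SD, assumed because the cited recommendation is not at hand) gives 28 per group. The sample size figures reproduce and are not in question.

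**Can length of stay be approximately normal?**
- Under N(13, 9.5), P(stay < 0) = Φ(−13/9.5) = Φ(−1.37) = 8.6%. Mean − 2 SD = 13 − 19 = −6 days.
- A symmetric single-peaked distribution on non-negative values with mean 13 must lie within 0 to 26 days, so its SD is at most 26/√12 = 7.5. The stated SD is 9.5, so a long right tail is needed.
- Simulation with assumed gamma and log-normal shapes (mean 13, SD 9.5): Shapiro-Wilk rejects normality in about 76% and 87% of samples of 28, and in 98% and 99.6% of samples of 56.
- Under the same shapes the median is about 10.8 and 10.5 days against a mean of 13. The mean and SD cannot be read back from median and IQR without assuming a shape.

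**What reporting the mean would give.** With 28 per group, the 95% CI half-width for the mean difference is 2.005 × 9.5 × √(2/28) = 5.1 days. A pooled SD of 9.5 on 54 degrees of freedom has a 95% CI of about 8.0 to 11.7 days. Both are normal-theory approximations.

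**Power for the 2-day target.** Two-sided 0.05: 12.1% with 28 per group and 12.9% with 31. By the half-width above, a t test reaches P < 0.05 only for an observed difference of about 5.1 days, which is 5.1/2 ≈ 2.5 times the target.

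**Number of comparisons.** The document gives no count, so two are shown.
- Postoperative only, complications counted as two: 2 (health status) + 2 (distress) + 2 + 1 (stay) + 1 (satisfaction) = 8.
- All three time points, complications counted as three (number, grade, index): 3 + 3 + 3 + 1 + 1 = 11.

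**Chance of at least one false positive, all nulls true.**

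| Pairwise correlation | 8 tests | 11 tests |
|---|---|---|
| 0 (formula 1 − 0.95^k) | 34% | 43% |
| 0.3 (simulated) | 30% | 37% |
| 0.5 (simulated) | 25% | 30% |
| 0.7 (simulated) | 19% | 22% |

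**Ordered complication grade.** If Clavien-Dindo grade is analysed as a category, the rule is "Categorical data will be compared using the" χ² test, with Fisher's test as fallback, and neither uses the order. In simulation with 31 per arm and an assumed seven-level control distribution (50/12/20/6/6/4/2%), power of the exact test against a rank test is about 33–36% against 55–57% at odds ratio 3, 16% against 28% at odds ratio 2, and 11% against 12% at odds ratio 1.5.

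**The case against.** The strongest reply is that this is openly a pilot. Its stated targets are participation and compliance rates, each test keeps its own 5% error, and exploratory outcomes do not generally require multiplicity adjustment. That stands, and no adjustment is asked for. It does not remove the need for a label: the significance sentence is unrestricted, and the Randomisation section speaks of adequate power for a primary-endpoint hypothesis although the Outcomes section names no primary endpoint.

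Several stronger readings are tempting but not supported:
- A reader might infer that the plan states length of stay will be shown by median and IQR. It does not name length of stay, and it does not forbid giving both summaries. The omission is a probable consequence of the rule, and a full protocol or SAP may add to it.
- A reader might infer that the SD is unknown and the later trial would be left without one. The Rationale speaks only of effect size, and the Sample size calculation supplies the centre's own SD. What is at risk is the trial's own mean difference and an updated SD in the randomised patients.
- A reader might infer that the other outcomes are only tested. They are also summarised. For those shown as mean ± SD or as counts, a difference and CI can be derived.
- A reader might count 26 tests, by adding five EQ-5D dimensions at three visits to the 11, and arrive at 1 − 0.95^26 = 74%. Nothing in the text says the dimensions are tested separately.
- A reader might infer a serious power loss for complications. The gap depends on an assumed grade distribution and nearly vanishes at an odds ratio of 1.5. The Comprehensive Complication Index, a numerical score, already falls under the t or Mann–Whitney rule.

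**Conclusion.** The point holds as a weakness in stated rules, not as an arithmetic error. On the protocol's own mean and SD, length of stay must be right-skewed unless its distribution is oddly shaped (not single-peaked). The either/or rule would therefore probably drop the mean difference, SD and CI that the pilot was sized on and that the Discussion says it should help estimate. How often a normality check would fail rests on the assumed gamma or log-normal shapes; the conflict between the SD and a symmetric shape does not.

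The unlabelled 5% rule applies to at least 8 postoperative comparisons. The 34% to 43% chance of a false positive assumes independence and all nulls true. Repeated instruments in the same patients and two scores from the same complications make correlation likely, so the true figure is probably lower (19% to 37% over the correlations tried). With about 12% power for the 2-day target, a significant length-of-stay result would be a poor guide to the effect. The change is worth making and is nearly free. The handling of complication grade is a minor, optional matter.

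**What to change.** In the Data analysis plan:

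1. For length of stay, always report mean and SD per arm and the mean difference with a 95% CI (for example by bootstrap), next to median and IQR, whatever the distribution.
2. Report clinical between-group differences as estimates with 95% CIs. Label all clinical P values exploratory and state that no conclusion of efficacy rests on P < 0.05.
3. Optionally, if Clavien-Dindo grade is compared across its ordered levels, use a rank test or a proportional-odds model in place of χ² or Fisher. The gain is small at modest odds ratios.

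The cost is a few sentences, slightly more output, and giving up claims of significance that a trial of this size could not support. Design, sample size and data collection do not change.

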#### Clinical outcomes

Difference in health status assessed with the EQ-5D-5L health questionnaire [31] preoperatively, 7 days after surgery and 30 days after surgery.Difference in the number and severity of postoperative complications between the study groups the Clavien-Dindo classification and *Comprehensive Complication Index*® (CCI) [32, 33]Difference in length of hospital stay between the two study groups.Difference in psychosocial distress preoperatively, at 7 days and at 30 days, assessed with the NCCN Distress Thermometer [34].Difference in patient satisfaction at discharge assessed with the EORTC IN-PATSAT 32 [35].

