### Methods against bias

#### Randomisation

The subjects will be randomised preoperatively to one of the two groups (VR fitness/control) in a concealed fashion. Study randomization will be performed through Study Randomizer (2017), a web-based randomization service, after all inclusion and exclusion criteria have been reviewed [38]. Allocation to the study groups is done in a 1:1 ratio. Block randomisation will be performed to ensure equal-sized groups. The size of the individual blocks will only be disclosed after the study has been completed so as not to allow prediction of group allocation. A sufficient number of subjects will be recruited according to the sample size calculation to prevent random errors and to ensure sufficient power to test the hypothesis of the primary endpoint. Randomisation is done by the staff of Augsburg University Hospital who are not involved in data collection and care of the study patients.

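### EQ-5D-5L and distress are measured before surgery, but the only group comparisons stated for days 7 and 30 are unadjusted, which gives up precision a baseline-adjusted model would recover

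*Protocol article*

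**What the plan says.** Under Clinical outcomes, the protocol article lists two questionnaire outcomes with a preoperative measurement: "Difference in health status assessed with the EQ-5D-5L health questionnaire [31] preoperatively, 7 days after surgery and 30 days after surgery" and "Difference in psychosocial distress preoperatively, at 7 days and at 30 days, assessed with the NCCN Distress Thermometer".

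Under Data analysis plan, the between-group methods for continuous variables are stated once, for all of them: "Approximately, normally distributed continuous variables will be compared using the independent" *t* test, and "Non-normally distributed continuous variables will be compared using the Mann–Whitney" *U* test. The threshold is "A two-sided *P* < 0.05 is considered significant". The section names no covariate, analysis of covariance or repeated-measures model. For EQ-5D-5L it adds only that scoring and reporting follow the instrument's user guide.

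Under Randomisation: "Allocation to the study groups is done in a 1:1 ratio", and "Block randomisation will be performed to ensure equal-sized groups". No stratification factor is named, so nothing stated in the design balances the arms on preoperative health status or distress.

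The Discussion justifies having a control arm partly by the better effect-size estimate it allows.

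**The concern.** Patients differ in health status and distress before surgery, and part of that difference usually persists to follow-up. A *t* test or Mann–Whitney test on the day-7 or day-30 score leaves that part in the error term. The preoperative questionnaire, already collected, could remove it.

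What is at stake is the width of the confidence intervals for these two outcomes. The Rationale section says that no data exist to estimate the effect size, and one purpose of the two-arm design is to supply such an estimate. In a pilot of this size the intervals will be wide, so a gain that needs no extra patients is worth taking.

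**Working it through.** **Inputs**
- Evaluable patients per group: 28 (Sample size calculation).
- Allocation: 1:1 (Randomisation).
- Correlation ρ between preoperative and follow-up score: not in the article. Assumed range 0.3 to 0.6.
- Results are in units of the outcome's SD, because the article gives no SD for EQ-5D-5L or distress. The SD is taken as equal in both arms.

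**The plan's own figure**
- 28 + 3 = 31 per group, and 2 × 31 = 62 in total. This reproduces.

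**Unadjusted comparison at one follow-up visit**
- SE = SD × √(2/n) = √(2/28) = 0.267 SD.
- The 95% CI half-width, using the *t* quantile on 54 degrees of freedom, is 0.54 SD.

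**Comparison adjusted for the preoperative value**
- SE = SD × √(2/n) × √(1 − ρ²).
- Proportional reduction in variance = ρ².
- Unadjusted group size giving the same precision = 28/(1 − ρ²).

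| ρ (assumed) | Variance reduction | Adjusted SE (SD units) | Equivalent n per group |
|---|---|---|---|
| 0.3 | 9% | 0.255 | 30.8 |
| 0.4 | 16% | 0.245 | 33.3 |
| 0.5 | 25% | 0.231 | 37.3 |
| 0.6 | 36% | 0.214 | 43.8 |

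Estimating the extra coefficient costs a factor of about √(1 + 1/(2 × 28 − 4)) = √(1 + 1/52) = 1.01 on the SE, or 1%. This does not alter the picture.

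**Is chance baseline imbalance a second, separate harm?** No. The unadjusted variance is 2/28 = 0.0714. At ρ = 0.5, the part due to chance imbalance is 0.25 × 0.0714 = 0.0179. The remainder is 0.0714 − 0.0179 = 0.0536, whose square root is 0.231, the adjusted SE in the table. The imbalance is therefore already inside the 0.267, and removing it is the precision gain.

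**Would change scores do as well?** The outcome wording could be read as change from the preoperative value. With equal SDs at both visits, the SE of a change-score comparison relative to the unadjusted follow-up comparison is √(2(1 − ρ)).

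| ρ (assumed) | Change score | Baseline-adjusted |
|---|---|---|
| 0.3 | 1.18 | 0.95 |
| 0.4 | 1.10 | 0.92 |
| 0.5 | 1.00 | 0.87 |
| 0.6 | 0.89 | 0.80 |

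Since 1 − ρ² = (1 − ρ)(1 + ρ) and 1 + ρ is less than 2 for any ρ below 1, the adjusted analysis is the more precise throughout. Below ρ = 0.5, change scores are less precise than ignoring the baseline.

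**The case against.** The strongest reply is that nothing here is an error. The unadjusted tests hold their type I error and the comparison is unbiased over randomisations. These are clinical outcomes in a pilot whose numerical targets concern participation and compliance and whose sample size rests on length of stay. The gain also depends on an unknown ρ. Baseline precedes major surgery and one follow-up is only a week after it, so a low correlation is possible; at ρ = 0.3 the SE falls by only about 5%. All of this stands and limits the weight of the point. It does not remove it, because the article states the method outright and the better one uses data already collected.

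Three stronger readings are tempting, but the document does not support them.

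- *A significance test at the preoperative visit is planned.* The outcome list includes that time point, and the general rule could be applied to it. No such test is stated, however, and the wording also allows comparison of changes.
- *A chance imbalance could swamp the planned effect.* A one-SD imbalance of 0.267 would shift the follow-up difference by 0.5 × 0.267 = 0.13 SD at ρ = 0.5, and a reader might set that against the standardised effect of 0.21. But 0.21 is 2/9.5 days, an effect on length of stay, which has no baseline value. The article gives no effect size for EQ-5D-5L or distress. Nor is a one-SD imbalance typical: the median absolute imbalance is 0.6745 × 0.267 = 0.18 SD, a shift of 0.09 SD at ρ = 0.5.
- *Adjustment is entirely free.* The inclusion criteria allow consent after emergency surgery, and such patients may have no preoperative score. A simple covariate model would drop them. Scores may also be far from normal, for which the plan now switches to a rank test. The fix has to cover both.

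**Conclusion.** The point holds as a matter of efficiency. For the two outcomes with a preoperative measurement, the stated tests are valid but less precise than a baseline-adjusted comparison. At 28 evaluable patients per group the SE would fall from 0.267 SD to between 0.255 SD (ρ = 0.3) and 0.214 SD (ρ = 0.6). That is a variance reduction of 9% to 36%, or the precision of about 31 to 44 patients per group.

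This rests on the assumed range for ρ, on a roughly linear relation between baseline and follow-up, and on 28 patients per group with usable follow-up scores. Reading the outcomes as change scores does not rescue the stated methods. The arithmetic applies to comparisons of means; it does not measure the gain over a Mann–Whitney test. Type I error, sample size, feasibility outcomes and the length-of-stay analysis are unaffected. The change is advisable, but the plan is not invalid without it.

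**What to change.** Amend the Data analysis plan for the EQ-5D-5L scores and the distress score:

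1. Estimate the between-group difference at days 7 and 30 from a linear or repeated-measures model with arm and the preoperative value. Report the adjusted difference with its 95% CI.
2. Keep patients who have no preoperative score because they consented after emergency surgery. Mean imputation of the baseline, or a longitudinal model with a common baseline mean for both arms, would do this. Name the chosen rule in advance.
3. If scores are clearly non-normal, use a rank-based or bootstrap version of the adjusted comparison.
4. Present preoperative scores by arm descriptively.

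The cost is a few sentences in the plan, a little extra analysis work and a rule for missing baselines. No new patients, visits or questionnaires are needed, and the total of 62 stands.

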## Discussion

Postoperative immobilisation and prolonged bed rest are important risk factors for postoperative surgical and non-surgical complications. As many patients require significant support after abdominal surgery, the provision of physiotherapy for this patient group is time-consuming and requires high staffing levels. Unfortunately, in many health systems, a lack of staff and financial resources prevent early and intensive mobilisation as recommended in many guidelines. Although the intervention investigated is currently not sufficient to replace conventional physiotherapy, it could help to increase the amount of physiotherapy per patient at a very low cost.

VR-based interventions are gaining ground in many different areas of medicine because they are easy to use and often inexpensive, especially compared to interventions that require more medical staff and equipment. Activity-promoting VR applications are not only a potential strategy to reduce sedentary lifestyles but have also been successfully used in neurorehabilitation of stroke patients, patients with paralysis and with Parkinson’s disease to improve cognitive functions, motor skills and balance [40]. Activity-promoting video games can be played on various systems such as gaming consoles, PCs and other devices. VR-based interventions with head-mounted devices can be performed in any location without the need to move the equipment or move the patient to another room, potentially providing a greater degree of flexibility. Currently, there is no data on the postoperative use of VR-based activity-enhancing video games to facilitate physical rehabilitation. Therefore, we initiated a pilot study to investigate the usefulness and feasibility of a VR-based intervention to improve recovery after colorectal cancer surgery.

Since the use of VR-based fitness games in the early postoperative phase could have positive effects on psychological well-being, we decided to assess distress and patient satisfaction in addition to health status as a clinical outcome.

In terms of feasibility, we aim to achieve a minimum participation rate of 70% and a minimum compliance rate of 80% in terms of the completion of questionnaires and participation in the VR sessions offered. Trial participation rates and participation in VR sessions will be analysed during the study. If necessary, the reasons for low attendance rates are analysed and strategies to improve recruitment and participation in the VR sessions offered are discussed with team members.

Although this is a pilot study, we opted for a two-arm design as this provides data from a control, allowing a better understanding of the effect of the study intervention and a more accurate estimate of effect size. Even though randomisation is not a mandatory element of pilot trials we decided to use randomisation to further improve data quality and reduce selection bias. Even though the exercises could be performed by the patient without assistance, we chose to use supervision, to ensure that all exercises are performed correctly, to guarantee adherence to the protocol and to make sure that patients have no problems with the handling of the VR headset. Depending on the results, supervision could be omitted in future trials, if patients are adequately introduced to the system. This could provide an even greater degree of flexibility. The trial intervention could be performed after any abdominal surgery, but we decided to focus on colorectal cancer patients as colorectal cancer surgery is a common procedure and we wanted to ensure a relatively homogeneous patient population.

The proposed pilot study will be the first step to evaluate the feasibility of VR-based interventions in the perioperative period, with the aim of improving the postoperative rehabilitation of cancer patients.

